### Economic analysis

Subsequent to the outcome analysis, we will conduct an economic analysis. The objective of the economic analysis will be to compare the relative costs and effects of a community paramedicine intervention with usual care. We will conduct the analysis from the perspective of the MOHLTC using data from the randomized controlled trial and ICES. Since the effectiveness outcomes are hospitalization, ED visits, primary care visits, EMS utilization and medication use, which can be expressed in monetary terms (for example, hospitalization cost), we will convert the outcomes to dollars and will analyze the costs of the two groups. Total cost for each patient includes the cost of intervention and the health care costs incurred within 1-year following randomization (as defined in the outcome measures sections). Based on initial intervention assignment, we will analyze the cost variable as a dependent variable to estimate the difference in expected health care cost with a study group as the primary independent variable in a regression model. Employing regression will allow for the adjustment of potential confounders (for example, patient characteristics).

In theory, an ordinary least squares (OLS) model produces unbiased estimates even if the data are skewed; [31] however, additional estimation methods (for example, generalized linear models [32]) and different uncertainty methods (for example, parametric and non-parametric confidence intervals) will facilitate careful investigation of the impact various assumptions have on our conclusions. In addition, we will conduct a cost-effectiveness analysis using mortality and QALY as the outcome of interest. Methods for censored cost and outcome data will be accommodated in a net benefit regression framework [33, 34].

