### Patient population

Patients of the participating family health teams diagnosed with either HF, COPD or DM will be screened for potential study eligibility by their primary care physician by applying search filters to the patients’ electronic medical records (EMR). Eligibility criteria are listed in Table 1. Patients will be deemed to be high-risk at the discretion of the primary care physician, based on (i) prior patterns of health care use, (ii) test results, (iii) compliance and (iv) clinical *gestalt*. Enrolled patients will be confirmed to be high-risk for admission by determining their rates of hospital admission over the 3 years prior to study enrollment, through linkage with the Institute for Clinical Evaluative Sciences (ICES) databases. Rates of admission will then be compared to previous literature to determine patients who are high-risk.

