### Proposed primary and secondary outcome measures

The primary outcome of this trial is the number of hospitalizations per patient after one year of study enrollment. Secondary outcomes will be measures of health system utilization at 1-year (reported as all cause and disease specific) and will include the following:Calls to 911 (regardless of whether patient was transported to hospital)Visits to the participating family health team clinics and any after-hours clinicsLength of stay in hospital if admittedMortalityOverall health status assessment using the (Euroqol-5D 3L) EQ-5D-3L measured at baseline and one year after study enrollment [19, 20]Measures of intervention compliance and safety (that is completed assessments and visits and protocol violations identified by physician review of EMR)Cost-effectiveness analysis for this model of care

The family health team electronic patient record data will be linked via the health card number to province-wide administrative health datasets held at the ICES, a section 45 Prescribed Entity under Ontario’s Personal Health Information Protection Act. Health services data at ICES represent ‘transactions’ of health care utilization, such as inpatient/outpatient hospital utilization, emergency room and other ambulatory clinic visits, drug claims for patients 65 and older, claims for physician services in any setting, and others. Linkage to the ICES administrative databases requires use of the Ontario health card number for each subject; following linkage, only the unique ICES encrypted identifier will remain on the files used for analysis. Linkage will allow us to obtain a more comprehensive view of specific health system utilization than could be achieved with unlinked data. Many disease-specific codes have been validated in ICES’ databases [21–23].

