### Outcome analyses

The MITT or efficacy population will consist of all eligible randomized patients who met all eligibility criteria and who received the full study protocol (4 scheduled paramedic visits over a 1-year period or patients randomized to the control group who remained in the study for the full 1-year period). Furthermore, this trial is intended to target patients with chronic disease who are at high-risk for admission to hospital. However, initial patient enrollment into the study was based upon family physician estimation of patient risk; therefore there is a possibility that some patients enrolled in the study do not represent a high-risk group for hospital admission. Patients enrolled in the trial will have their risk of admission assessed based on their actual rates of admission over the previous 3 years. This information will be gathered through linkage with the ICES databases. Cut-off values for low, medium and high-risk categories will be calculated based on a review of the literature and clinical expertise. Only those patients who are determined to be high-risk will be included in the MITT analysis. Conversely, the ITT or effectiveness population includes all patients randomized regardless of their eligibility, adherence to study protocol or calculated risk of admission.

The primary analysis will be done using an ITT analysis. Baseline characteristics of patients in the intervention and control groups within each disease-specific group will be reported using descriptive statistics, mean/SD or median/IQR for continuous variables and count/percent for categorical as appropriate. Tests of significance will be performed using *t*-tests or Wilcoxon rank-sum test for continuous variables and chi-square or Fisher’s exact test (expected counts < 5) for categorical variables as appropriate. Two-sided *P*-value < 0.05 will be used to determine significant differences in baseline characteristics. These analyses are useful not only to assess the comparability of the treatment group but also to describe the sample of subjects who entered the trial. Test of normality for each variable will be determined using the Shapiro-Wilk test *P*-value < 0.05. All tests will be two-sided and carried out at a significance level at 5%.

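### The cost regression treats covariates only as a guard against confounding and leaves prior health care use and the disease stratum unnamed; fixing both in advance could sharpen this secondary analysis at little cost

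*Protocol article*

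**What the plan says.** The Economic analysis section defines the outcome as follows: "Total cost for each patient includes the cost of intervention and the health care costs incurred within 1-year following randomization". Costs are seen "from the perspective of the MOHLTC using data from the randomized controlled trial and ICES". The model, by initial assignment, is to "estimate the difference in expected health care cost with a study group as the primary independent variable in a regression model". On covariates it says only: "Employing regression will allow for the adjustment of potential confounders (for example, patient characteristics", and the example closes there. The section goes on to ordinary least squares, generalised linear models, interval methods and net-benefit regression, but names no covariate.

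Two baseline items that could serve are described elsewhere in the article:

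- **Prior admissions.** Under Patient population, enrolled patients are to be "confirmed to be high-risk for admission by determining their rates of hospital admission over the 3 years prior to study enrollment", through ICES linkage. Outcome analyses repeats this: "Patients enrolled in the trial will have their risk of admission assessed based on their actual rates of admission over the previous 3 years". The stated uses are risk classification and selection of the modified intention-to-treat population. The Sample size section adds a check of the planned number against ICES baseline admission rates.
- **Disease stratum.** Recruitment and randomization allocates 1:1 in blocks within disease group, on the ground that disease characteristics may influence the outcome.

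The outcome-measures section describes ICES holdings as including "inpatient/outpatient hospital utilization, emergency room and other ambulatory clinic visits", together with physician claims, and with drug claims for patients aged 65 and older.

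**The concern.** Under randomisation, study group is not systematically related to any baseline factor, so confounding is not the main reason to put covariates in the cost model. Their main value is to explain between-patient variation in cost and so narrow the interval for the cost difference. The stated rationale therefore steers the analyst towards a less useful selection criterion. It also leaves open that covariates are chosen after costs have been seen.

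On the protocol's own logic, prior use is a natural candidate. Past admissions are its measure of future admission risk, and hospitalisation is the first item to be priced. The article also concedes that some enrolled patients may turn out not to be high-risk, so prior use should vary within the intention-to-treat population. The disease stratum is a second candidate, since the randomisation is built on it.

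At stake is the width of the interval for the cost difference and for the net-benefit result. The sample size was set for admissions, and no power is given for cost.

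**Working it through.** **The plan's own figure.** Inputs from the Sample size section: rate ratio 0.85, baseline rate 1.85, over-dispersion 1.0, R-squared 0.05, 80% power, 0.05 significance level. Outcome analyses states that tests are two-sided. For a Poisson regression on a binary 1:1 covariate:

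N = [1.96 × √4 + 0.842 × √(2 + 2/0.85)]² / (1.85 × (ln 0.85)²) / (1 − 0.05) = 659.3 / 0.95 = 694.0

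The stated figure is 695, and power at 695 is 80.05%, so the figure reproduces. It concerns admission counts and says nothing about cost precision. Its R-squared of 0.05 relates study group to the other covariates; it is not the covariate–cost correlation needed here.

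**Precision gain from a prior-use covariate.** Let r be the correlation between the covariate and follow-up cost. In a linear model with study group and this one covariate:

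- residual variance is multiplied by 1 − r²;
- the standard error of the cost difference is multiplied by √(1 − r²);
- 695 adjusted patients are worth 695 / (1 − r²) unadjusted patients.

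For power, take the difference that has 80% power without adjustment at 348 per group: (1.96 + 0.842) × √(2/348) = 0.212 cost SDs.

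The article gives no r, so a range is assumed:

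| r (assumed) | Standard error ratio | Unadjusted N equivalent to 695 | Power for 0.212 SD |
|---|---|---|---|
| 0.2 | 0.98 | 724 | 82% |
| 0.3 | 0.95 | 764 | 84% |
| 0.4 | 0.92 | 827 | 86% |
| 0.5 | 0.87 | 927 | 90% |
| 0.6 | 0.80 | 1,086 | 94% |
| 0.7 | 0.71 | 1,363 | 98% |

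**The same loss seen as chance imbalance.** The difference between arms in the mean of a baseline variable has standard deviation √(2/348) = 0.076 SDs, so 95% of trials fall within ±1.96 × 0.076 = ±0.149. A fraction r of this carries into an unadjusted cost difference: ±0.03 SD at r = 0.2 and ±0.10 SD at r = 0.7. This is part of the sampling variance already counted in the table and must not be added to it.

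**What is not quantified.** The article has no figure from which to compute the gain from the disease stratum. The table's comparator has no prognostic covariates, so the gain is smaller if the unnamed patient characteristics already reflect prior use or severity. Gains in generalised linear models and net-benefit regression may differ from the linear case.

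**The case against.** The strongest reply is that a condensed article may leave the covariates of a secondary economic regression to the full protocol or an economic analysis plan, and that nothing here is false or contradictory. That stands as far as the missing list goes: its absence alone would be no finding. What remains is narrower. The section does state a purpose for adjustment, that purpose is not the useful one in a randomised comparison, and a suitable baseline value and the strata are already part of the trial. It is fair to answer that *confounders* is often used loosely for baseline covariates; the word alone does no harm to the planned regression.

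Three stronger readings are tempting, and the article does not support them:

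- *The cost model leaves prior use out.* The example is open-ended, and prior admissions could count as a patient characteristic. The text neither includes nor excludes them.
- *Prior cost is already linked and comes free.* The planned look-back is of admissions, "determining their rates of hospital admission over the 3 years prior to study enrollment", not of costs or of other kinds of use. The description of ICES holdings is general and plans no pre-enrolment cost extraction. Medication use is to be priced, but ICES drug claims are described only for patients 65 and older.
- *Without adjustment, chance imbalance biases the result.* It does not. A valid unadjusted interval already covers it, so imbalance and interval width are one loss, not two.

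**Conclusion.** The point holds as a modest improvement to a secondary analysis. The Economic analysis section justifies covariates by confounding alone and does not name the two baseline items the trial already plans to have: the three-year pre-enrolment admission rate and the randomisation stratum. Fixing them in advance would reduce the standard error of the cost difference by about 2% if r is 0.2, 13% if r is 0.5 and 29% if r is 0.7.

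These sizes rest on an assumed r, a linear model and a comparator without other prognostic covariates, so the true gain cannot be read from the article. The unadjusted estimate is valid either way.

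**What to change.** In the Economic analysis section, state that the cost regression and the net-benefit regression include, as covariates fixed in advance and chosen for precision:

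1. the disease stratum used for randomisation; and
2. each patient's pre-enrolment ICES admission rate over the three years already planned for linkage, or prior ICES cost if that is extracted and priced.

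Report the unadjusted cost difference alongside.

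The cost is about one sentence of text and a little more analysis work; with prior admissions, no new patient data are needed. Choosing prior cost instead requires further extraction and pricing, and the drug component would be available from ICES only for patients 65 and older.

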Patients will be asked about health-related quality of life using the EQ-5D-3 L, [20] a validated measure of quality-adjusted life years (QALY). QALY, a preference-based utility measure, incorporates both length of life and quality of life into a single measure. To estimate QALYs, we will convert EQ-5D data collected in the study to utility score using a validated algorithm [19] so no additional data collection will be required. Health-related quality of life assessments will be performed at baseline and 1-year after study enrollment. Assessments will be performed by the community paramedics for patients enrolled in the intervention cohort and by the patients’ primary care physicians in the control cohort.

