The primary outcome, number of hospital admissions over 1 year will be compared by group using both Poisson regression and negative binomial regression analyses. The goodness of fit of both models will be evaluated using Akaike’s information criterion (AIC) statistics. If, in spite of randomization, differences in baseline characteristics are found using bivariate analytical strategies, these variables will be included in the regression model. Multiple imputation algorithms will be developed in order to determine values for any missing data points [30].

The secondary outcome measures, which are largely count measures, will be compared between control and intervention groups using similar Poisson regression and negative binomial models. The proportion of patients who die during the study period will be compared for the intervention and control groups within each disease-specific group using chi-square tests as well as a logistic regression model, adjusting for any potential confounding variables as appropriate.

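### Baseline EQ-5D utility is not prespecified as a covariate for the EQ-5D, QALY and net-benefit comparisons, although with only two readings it carries half the weight of a survivor's QALY

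*Protocol article*

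**What the plan says.** **Timing.** Under Proposed primary and secondary outcome measures, EQ-5D-3L is a secondary outcome "measured at baseline and one year after study enrollment". The same section repeats: "Health-related quality of life assessments will be performed at baseline and 1-year after study enrollment". No intermediate reading is planned.

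**From EQ-5D to QALY.** "To estimate QALYs, we will convert EQ-5D data collected in the study to utility score using a validated algorithm". The article does not say how the two utilities are combined into a QALY, or how deaths enter.

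**Economic model.** Economic analysis makes mortality and QALY the effects in the cost-effectiveness analysis ("In addition, we will conduct a cost-effectiveness analysis using mortality and QALY as the outcome of interest") and adds: "Methods for censored cost and outcome data will be accommodated in a net benefit regression framework". Its one sentence on adjustment follows the description of the cost regression: "Employing regression will allow for the adjustment of potential confounders (for example, patient characteristics"). Baseline utility is neither named nor excluded.

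**Covariate rule for outcomes.** Outcome analyses states, in the paragraph on the primary outcome: "If, in spite of randomization, differences in baseline characteristics are found using bivariate analytical strategies, these variables will be included in the regression model". The criterion for a baseline difference in that section is a two-sided P below 0.05. Secondary outcomes, described there as mostly counts, "will be compared between control and intervention groups using similar Poisson regression and negative binomial models".

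**The concern.** Baseline utility is a component of a two-reading QALY. It is also likely to be the strongest predictor of the one-year utility. Whether it enters the model should therefore not depend on a baseline significance test, yet such a test is the only concrete covariate rule in the article, and it reaches EQ-5D through the reference to similar models. The economic section leaves the choice open under a general reference to confounders.

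Two things are at stake. Leaving baseline utility out gives up precision that the trial has already paid to collect. And if the choice is made after the data are seen, the cost-effectiveness conclusion could depend on it.

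**Working it through.** **The plan's own figure.** The article gives no SD, correlation or power for EQ-5D or QALY. Its only size calculation is for hospitalizations: 695 patients, rate ratio 0.85, baseline rate 1.85, phi 1.0, R-squared 0.05, two-sided 5%, 80% power. The Poisson-regression formula gives N = (1.96 × √4 + 0.8416 × √(2 + 2/0.85))² / (1.85 × (ln 0.85)² × 0.95) = 32.215 / 0.04642 = 694.0, so 695 reproduces. That figure is not affected by this point.

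**Inputs.** From the article: two EQ-5D readings, about 348 per arm, one-year mortality of 4.4% (COPD), 8.2% (DM) and 10% (HF). Assumed: correlation ρ between baseline utility u0 and one-year utility u1 of 0.3 to 0.7; SD s = 0.25 at both times; mean utility 0.7; a true one-year gain of 0.05, which is 0.025 QALY.

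**1. QALY, survivors.** With Q = (u0 + u1)/2:
- Unadjusted variance = s²(1 + ρ)/2.
- Variance given u0 = s²(1 − ρ²)/4.
- Ratio = (1 − ρ)/2 = 0.35, 0.25, 0.15 at ρ = 0.3, 0.5, 0.7, a cut of 65%, 75%, 85%.

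**2. QALY with deaths.** Let a fraction m die at times uniform over the year, independent of utility. A patient who dies at time T contributes c × T × u0, with c = 1 if utility holds at baseline until death and c = 1/2 if it falls linearly to zero at death. The proportional cut is Cov(Q,u0)² / (s² Var Q), where
- Cov(Q,u0)/s² = mc/2 + (1 − m)(1 + ρ)/2,
- E(Q) = 0.7 × (mc/2 + 1 − m),
- E(Q²) = (mc²/3)(0.49 + 0.0625) + (1 − m)(0.49 + 0.0625(1 + ρ)/2).

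Low end (m = 0.10, c = 1/2, ρ = 0.3): Cov/s² = 0.610; Var Q = 0.4822 − 0.6475² = 0.0629; cut = 0.610² × 0.0625/0.0629 = 37%.

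High end (m = 0.044, c = 1, ρ = 0.7): Cov/s² = 0.8346; Var Q = 0.5273 − 0.6846² = 0.0587; cut = 0.8346² × 0.0625/0.0587 = 74%.

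**3. One-year EQ-5D.** The cut is ρ²: 9%, 25%, 49%.

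**4. Net benefit.** With cost independent of utility, ρ = 0.5 and deaths ignored, the variance ratio is (λ² × 0.01172 + SDc²) / (λ² × 0.04688 + SDc²). For cost SD from 5,000 to 20,000 it is 0.38 to 0.83 at λ = 50,000 per QALY and 0.29 to 0.60 at λ = 100,000. The cut is therefore 17% to 71%.

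**5. Power for the QALY difference, survivors.** The SE of a mean utility difference is 0.25 × √(2/347.5) = 0.0190. At ρ = 0.5, power for 0.025 QALY is 33% unadjusted and 86% adjusted (37% and 79% at ρ = 0.3; 30% and 96% at ρ = 0.7).

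**6. The significance trigger.** If baseline utility entered only when one pooled test gave P < 0.05, simulation (348 per arm, 5,000 runs) gives QALY variance of 0.81, 0.77 and 0.75 of unadjusted at ρ = 0.3, 0.5 and 0.7, against 0.35, 0.25 and 0.16 with fixed adjustment. Simulated power at ρ = 0.5 (347 per arm, 4,000 runs) is 34% under the trigger, 33% unadjusted and 86% with fixed adjustment.

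**7. Chance imbalance.** The largest unflagged baseline difference is 1.96 × 0.0190 = 0.037. It moves the expected QALY difference by 0.037 × (1 + 0.5)/2 = 0.028. That is the edge of the test, not a typical imbalance. Over repeated randomizations the simulated mean difference is about zero with or without adjustment.

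**8. Assessor shift d between arms.** The adjusted QALY bias equals the unadjusted bias minus (1 + ρ)/2 times the baseline shift.

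| Shift present at | QALY unadjusted | QALY adjusted | One-year EQ-5D unadjusted | One-year EQ-5D adjusted |
|---|---|---|---|---|
| Both times | d | d(1 − ρ)/2 | d | d(1 − ρ) |
| Baseline only | d/2 | −ρd/2 | 0 | −ρd |
| One year only | d/2 | d/2 | d | d |

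For the QALY, adjustment is never worse in size. For one-year EQ-5D it is worse if the shift is at baseline only.

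**The case against.** The strongest reply is that this is a condensed article, and a QALY formula and economic covariate list usually sit in the full protocol or analysis plan. Nothing excludes baseline utility. Net-benefit regression can carry it, and the economic section's adjustment wording has no P-value trigger. The significance rule itself is written for the primary outcome and reaches EQ-5D only through the reference to similar models.

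Much of that stands, and it limits the point. A reader might infer that no planned comparison adjusts for baseline EQ-5D. The article supports only that such adjustment is not prespecified. A reader might also infer that baseline utility would enter about 1 time in 20. But the economic section has no such trigger, and Outcome analyses describes the baseline comparison within each disease group. A flag in any of three groups would arise by chance with probability 1 − 0.95³, about 14%.

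What does not stand is that this is only missing detail. The article does state a covariate rule, it is a poor one for this outcome, and an analysis plan that followed it would recover little of the precision available.

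A further objection concerns the fix. EQ-5D is assessed by paramedics in the intervention arm and by primary care physicians in the control arm, and Trial status describes the first paramedic visit as following randomization. The baseline reading may therefore be taken after allocation by unblinded assessors who differ by arm. This is a real caveat, and it is why unadjusted results should stay in the report.

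**Conclusion.** The point holds as a gap in prespecification combined with a weak stated rule. Fixed adjustment for baseline utility would cut the variance of the QALY difference by about 65-85% among survivors and about 37-74% with 4.4-10% mortality. It would cut one-year EQ-5D variance by 9-49% and net-benefit variance by about 17-71%. These sizes rest on a trapezoidal QALY and on an assumed ρ, utility mean and SD, death-time pattern, cost SD and willingness-to-pay. None of these is in the article.

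Two stronger readings are not supported. One is that the cost-effectiveness result must lose most of its precision: that fits the survivor QALY difference, but deaths and cost variance dilute it. The other is that chance baseline imbalance biases the result: under randomization it does not on average, though it moves the realized estimate and widens its uncertainty. The primary outcome and its sample size are untouched. The change is worth making but is not critical.

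**What to change.** In Outcome analyses, state that one-year EQ-5D utility is analysed by a linear model with treatment group and baseline EQ-5D utility. In Economic analysis, state that the QALY and net-benefit regressions always include baseline EQ-5D utility, whatever the baseline test shows. State also how the two readings and deaths form the QALY. Report unadjusted estimates of all three as a sensitivity analysis.

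The cost is wording only, since the baseline reading is already planned. There are two downsides. Missing baseline values must be imputed, which the existing multiple-imputation plan can cover. And an assessor difference present only at baseline would bias the adjusted one-year EQ-5D comparison by −ρd where the unadjusted one has no bias, so both estimates should be shown and any disagreement discussed.
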